# Rehabilitation for life: the effect on physical function of rehabilitation and care in older adults after hip fracture—study protocol for a cluster-randomised stepped-wedge trial

**DOI:** 10.1186/s13063-022-06321-w

**Published:** 2022-05-07

**Keywords:** Hip fracture, Rehabilitation, Care, Between sectors, Empowerment, Physical function, Stepped-wedge cluster randomised controlled trial

## Abstract

**Background:**

A hip fracture is a serious event for older adults, given that approximately 50% do not regain their habitual level of physical function, and the mortality rate is high, as is the number of readmissions. The gap in healthcare delivery, as separated into two financial and self-governing sectors, might be a contributing cause of inferior rehabilitation and care for these patients. Therefore, we aim to assess the effect of continuous and progressive rehabilitation and care across sectors for older adults after hip fracture.

**Methods/design:**

The project is designed as a stepped-wedge cluster randomised controlled trial. The study population of patients are older adults 65 years of age and above discharged after a hip fracture and healthcare professionals in primary and secondary care (municipalities and hospitals). Healthcare professionals from different sectors (hospital and municipalities) will be engaged in the empowerment-orientated praxis, through a workshop for healthcare professionals with knowledge sharing to the older adults using a digital health application (app). The rehabilitation intervention consists of 12 weeks of progressive resistance exercises initiated 1–2 days after discharge. To improve communication across sectors, a videoconference involving the patient and physiotherapists from both sectors will be conducted. On day, 3 after discharge, an outreach nurse performs a thorough assessment including measurement of vital signs. A hotline to the hospital for medical advice is a part of the intervention. The intervention is delivered as an add-on to the usual rehabilitation and care, and it involves one regional hospital and the municipalities within the catchment area of the hospital. The primary outcome is a Timed Up and Go Test 8 weeks post-surgery.

**Discussion:**

Using a stepped-wedge design, the intervention will be assessed as well as implemented in hospital and municipalities, hopefully for the benefit of older adults after hip fracture. Furthermore, the collaboration between the sectors is expected to improve.

**Trial registration:**

The study is approved by the Regional Scientific Ethics Committees of Southern Denmark (S-20200070) and the Danish Data Protection Agency (20-21854). Registered 9 of June 2020 at ClinicalTrials.gov, NCT04424186.

**Supplementary Information:**

The online version contains supplementary material available at 10.1186/s13063-022-06321-w.

## Background and rationale

A hip fracture is a serious event for older adults since approximately 50% do not regain their habitual level of physical function thus, acquiring new or additional need for care [1, 2]. Furthermore, when compared to an age-matched group, the 1-year mortality increases threefold and the quality of life is reduced [2, 3]. The 30-day readmission rate after a hip fracture is as high as 16–19% [4, 5].

For older adults, it is well-known that poor mobilisation and reduced activity during and after hospitalisation trigger loss of muscle mass that moreover is associated to increased mortality [3]. To reduce mortality, early detection of illness and sufficient pain management has been identified as important **[**6**,**
7**]**. Insufficient pain management is associated to an increased risk of complications, morbidity, and mortality and also impedes physical activity [8]. Nevertheless, continuous and progressive rehabilitation, as well as the detection of critical illness and complications, is lacking across the sectors in a healthcare system divided into two financial and self-governing sectors.

In Denmark, the average length of stay is 5–7 days for hip fracture patients [7]. Rehabilitation in the primary sector must be initiated within 7 days after discharge. However, usual care does not include systematic assessment including vital signs measurement. Furthermore, various exercise regimes are used depending on the sectors, and the regimes are usually not specified in terms of intensity or progression. Communication and cooperation between sectors are also lacking, although the older adults express a need for increased involvement [9].

To impede functional decline and lower mortality and readmission rates, continuous and progressive rehabilitation and care across sectors are needed. This study introduces an empowerment-orientated praxis focusing on continuous rehabilitation and care, as well as optimised communication and cooperation between sectors.

### Objective

This study aims to assess the effect of continuous and progressive rehabilitation and care across sectors for older adults following a hip fracture.

### Trial design

The protocol describes a cluster randomised stepped-wedge trial. It has a superiority design, a 1:1 allocation ratio, and the time interval for each step is set to three months, as illustrated in Fig. 1. The study protocol follows the Standard Protocol Items: Recommendations for Interventional Trial (SPIRIT) checklist (see Additional file 1) [10, 11]. A trial registration dataset is reported in Table 1.

**Fig. 1 Fig1:**
[figure not shown]
Overview of the clusters and the crossover from control to intervention

## Methods

### Study setting

The trial will involve a regional hospital in Denmark and all six municipalities in the hospital’s catchment area. The municipalities serve a mixed urban and rural population. Two of the municipalities will be divided into two clusters, and four smaller municipalities were combined to two clusters to account for the unequal population size. Services within hospitals and municipalities are free of charge in Denmark, and the responsibility for rehabilitation is shared between sectors [12]. At the time of discharge, older adults with a medically assessed need for rehabilitation are offered a referral for municipal rehabilitation [12]. A list of study sites can be obtained on request from the corresponding author.

### Eligibility criteria

The trial will include older adults 65 years of age and older, admitted to the ortho-geriatric ward with a hip fracture and residing in one of the municipalities. Other inclusion criteria are patients able to speak and understand Danish and orientated in time and place. Patients discharged to permanent residence in nursing homes or patients with competing diseases disabling relevant conversation, such as progressed dementia, or receiving palliative care, will be excluded.

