### Who will take informed consent

Assessment of eligibility and informed consent was obtained up to 72 h post-surgery, by trial data collectors. In cases where cognitive function was medically unresolved, decisions on inclusion were done in discussions with nurses and physiotherapists at the ward and patients’ next of kin. Prior to obtaining written consent, patients will receive written and oral information as required by the regional ethics committee. The consent form developed by the national ethics committee in Denmark was used.

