### Implementation

After agreeing to participate, patients are assigned pending on home addresses. Patients’ home address will be concealed until informed consent was obtained and prefracture baseline data collected. The data collector will inform the patient of the assigned group.

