### Methods in analysis to handle protocol non-adherence and any statistical methods to handle missing data

The analyses of outcomes follow the intention-to-treat principle. Missing outcomes will be imputed with multiple imputation [41]. For non-adherence to protocol, non-response analyses will be performed for excluded patients and non-completers. A per-protocol analysis will be conducted as a sensitivity analysis.

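### The nursing-home exclusion is worded on discharge destination, so for placements decided after the group is known it could remove allocated patients, contrary to intention to treat

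*Protocol article*

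**What the plan says.** Under Eligibility criteria, the article excludes "Patients discharged to permanent residence in nursing homes or patients with competing diseases disabling relevant conversation". The nursing-home part is expressed through discharge. Nothing in the article says that it means prefracture residence or the destination expected at screening.

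Under Who will take informed consent: "Assessment of eligibility and informed consent was obtained up to 72 h post-surgery, by trial data collectors".

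Under Implementation: "After agreeing to participate, patients are assigned pending on home addresses". The patient's "home address will be concealed until informed consent was obtained and prefracture baseline data collected", and then "The data collector will inform the patient of the assigned group". Table 3 likewise places allocation before the in-hospital and at-discharge measurements.

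Background and rationale states that in Denmark "the average length of stay is 5–7 days for hip fracture patients". The blinding section says that neither health professionals nor assessors can be blinded.

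On the analysis set: "The analyses of outcomes follow the intention-to-treat principle". The same section plans multiple imputation for missing outcomes and a non-response analysis for excluded patients and non-completers. It does not say how a patient who meets an exclusion criterion after consent is handled.

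**The concern.** Concealing the address until consent protects only the decisions taken before the address is seen. An eligibility rule that depends on something decided later falls outside that protection. A patient may consent, be assigned and be told the group, and only afterwards be placed permanently in a nursing home. Read literally, the criterion then makes that patient ineligible.

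If such patients are removed, and the chance of placement or its recording differs between conditions, the retained groups are no longer comparable. Those removed are likely to have poor mobility, which is what both primary outcomes measure. If they count as excluded rather than as missing, the planned multiple imputation does not reach them.

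A difference between conditions is conceivable because one ward serves all clusters and staff know the group. Knowing that a patient will receive five early sessions and a nurse visit at home could influence a borderline placement. Whether the intervention also acts before discharge is unclear: the Intervention description speaks of the programme in both sectors, while the abstract starts the exercises after discharge. Those passages should be reconciled.

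**Working it through.** **1. Order of events**

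| Event | Timing | Place in the article |
|---|---|---|
| Eligibility and consent | up to 72 h (day 3) after surgery | Who will take informed consent |
| Address revealed, patient told the group | after consent and prefracture baseline data | Implementation |
| Discharge | about day 5–7, a national average | Background and rationale |
| Nursing-home exclusion as worded | at discharge | Eligibility criteria |

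Interval with the group known and the destination possibly open: 5 − 3 = 2 days to 7 − 3 = 4 days. This is approximate. The stay is not this ward's figure, consent may come before 72 h, and length of stay and time since surgery need not start on the same day.

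**2. The plan's own figure**

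The Sample size section states 89% power for TUG. Inputs from the article: six clusters; 21 months in 3-month steps = 7 periods; 6 patients per cluster-period; SD 9.2 s; ICC 0.01; α 0.05; effect 0.25 × 21.1 = 5.275 s. Assumed: two-sided test, one cluster crossing per step.

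Hussey–Hughes variance, with I = 6, T = 7, U = 21, W = 91, V = 91:

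- σ² = 0.99 × 9.2² / 6 = 13.966; τ² = 0.01 × 9.2² = 0.846
- Var = Iσ²(σ² + Tτ²) / [(IU − W)σ² + (U² + ITU − TW − IV)τ²] = 6 × 13.966 × 19.890 / (35 × 13.966 + 140 × 0.846) = 2.745
- SE = 1.657 s; power = Φ(5.275/1.657 − 1.96) = 89.0%

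The stated 89% is reproduced. If a further 5%, 10% or 15% of the six patients per cell were removed after allocation (assumed rates), power would be 87.5%, 85.9% or 84.1%. Loss of power is therefore the smaller issue, and selection matters more.

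**3. Illustrated bias on CAS = 6, no true effect**

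Assumptions: 10% excluded in control and 5% in intervention. CAS = 6 is reached by 70% of the 90% who would be retained in either condition, and by 10% of the borderline 5% retained only in the intervention condition.

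- Control, retained: 70%
- Intervention, retained: (0.90 × 0.70 + 0.05 × 0.10) / 0.95 = 0.635 / 0.95 = 66.8%
- Spurious difference: about −3 percentage points

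**4. Illustrated bias on TUG, no true effect**

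Assume that excluded patients are D seconds slower than retained patients, with D from 5 to 15 s. The retained mean is then the overall mean minus p × D, where p is the proportion excluded. The spurious difference (intervention minus control) is (p_control − p_intervention) × D.

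| Excluded, control v intervention | D = 5 s | D = 10 s | D = 15 s |
|---|---|---|---|
| 5% v 5% | 0 | 0 | 0 |
| 10% v 5% | +0.25 s | +0.50 s | +0.75 s |
| 15% v 5% | +0.50 s | +1.00 s | +1.50 s |
| 5% v 10% | −0.25 s | −0.50 s | −0.75 s |

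Against the planned 5.275 s, the 10% v 5% case is 0.25/5.275 = 5% to 0.75/5.275 = 14% of the effect. A positive shift works against the intervention and a negative one favours it.

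**The case against.** The strongest reply is that the criterion is meant for the screen. The article places eligibility assessment, with consent, before the address is revealed, and the neighbouring criteria (age, language, orientation, advanced dementia, palliative care) are all facts available at that point. The nursing-home phrase can be read as expected destination. Permanent residents and patients with a placement already planned can be identified within 72 h. This stands. A reader might infer that the criterion can be applied only after allocation, and the documents do not support that. The problem is confined to placements decided later.

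A reader might also infer that allocated patients are in fact dropped. No section says so. The excluded patients who get a non-response analysis may simply be those excluded at screening. This stands too: the conflict with intention to treat arises if the rule is applied as written, and is not a reported practice.

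Third, the mechanism and the rates are not documented. The article does not say who decides placement, most intervention components are dated from discharge, control patients with an assessed need are also offered municipal rehabilitation, and the population is oriented and able to consent. A halving of permanent placement may be generous. This limits the claim about size but not the claim about wording.

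Finally, an article leaves detail to the full protocol. That covers how exclusions are operationalised. It does not cover a criterion that is stated, and stated on an event that normally follows disclosure of the group.

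**Conclusion.** The point holds as a defect in a stated rule. For new nursing-home placements, the criterion depends on an event that normally follows consent and disclosure of the group in an unblinded trial. Applied literally, it would remove allocated patients, contrary to the article's intention-to-treat principle.

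Its size cannot be established. The illustrated shifts (about 3 points on CAS = 6, 0.25–0.75 s on TUG at 10% v 5%) rest wholly on assumed rates and should not be read as estimates of bias. The direction is open, and the shift vanishes in these illustrations when exclusion is equal. On these assumptions it is modest beside the planned 5.275 s. The correction is still worth making because it costs little and removes an avoidable route to selection.

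**What to change.** 1. Define the criterion by facts fixed before allocation: permanent nursing-home residence before the fracture, or a permanent placement plan documented before the home address is revealed.
2. Keep every consented and allocated patient in the intention-to-treat set whatever the later destination, with missing outcomes handled by the planned multiple imputation.
3. Report discharge destination, and any exclusions after consent, by condition and step.
4. If post-consent exclusions have already been made, report them in the same way. Where consent allows, obtain readmission and mortality for those patients from records; the article already provides for consent to collect information from medical records.

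The cost is a change of wording and a few more patients to follow, some of whom will have no TUG. The planned power calculation does not change. If recruitment has ended (planned completion 30 October 2022), items 2 to 4 can still be done.

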### Who will take informed consent

Assessment of eligibility and informed consent was obtained up to 72 h post-surgery, by trial data collectors. In cases where cognitive function was medically unresolved, decisions on inclusion were done in discussions with nurses and physiotherapists at the ward and patients’ next of kin. Prior to obtaining written consent, patients will receive written and oral information as required by the regional ethics committee. The consent form developed by the national ethics committee in Denmark was used.

### Additional consent provisions for collection and use of participant data and biological specimens

Data will be collected in accordance with the Danish Data Protection Agency (20-21854). As required by Danish legislation, written informed consent will be obtained from participants to permit the collection of information from medical records.

### Intervention

#### Usual rehabilitation and care in the primary and secondary sectors

After admission to the emergency department, patients with a hip fracture are transferred to an ortho-geriatric ward. During hospitalisation, the patients are examined by an orthopaedic surgeon and a geriatric specialist. Mobilisation and rehabilitation are initiated within 24 h post-surgery and performed along with vital signs measurement for the early detection of critical illness and complication, throughout the entire hospitalisation period. A physiotherapist is responsible for rehabilitation which comprises walking, exercise, and instruction to a self-training programme. The Cumulated Ambulation Score (CAS) [13] is assessed daily and the need for walking aids is continuously evaluated. The rationale for usual praxis during admission is that early mobilisation and exercise, as well as early detection of critical illness, provide an optimal basis for regaining walking ability and reducing mortality. In the primary sector, usual rehabilitation varies in both content and setting. Content can vary in frequency of rehabilitation sessions and in focus of the session (e.g. gait, walking on stairs, and sit-to-stand at home) [9]. Rehabilitation is typically twice a week, completed in the patients’ own home or at a rehabilitation centre and with a duration of 6–8 weeks [9]. Rehabilitation can be supplemented with restorative care aimed to maintain activities of daily living (ADL). In both rehabilitation and restorative care, the older adults’ motivation is obtained by exercising specific ADL tasks. Care in the primary sector follows the plan prescribed by the hospital, and treatment changes have to be prescribed by the general practitioner.

#### Intervention description

The intervention will be offered to the intervention group in addition to the usual rehabilitation and care. The intervention is comprehensive and includes rehabilitation, empowerment, and care. The duration of the intervention will be 12 weeks (post-surgery). The basis for the intervention is that continuous and progressive rehabilitation, as well as early detection of critical illness and complication during and after hospitalisation, will improve the older adults’ physical performance. The older adults are expected to be motivated by an empowerment-orientated praxis [14].

Within the first 2 weeks after discharge, rehabilitation in the primary sector comprises five rehabilitation sessions. This will be followed by supervised rehabilitation twice a week for another 10 weeks. The rehabilitation in both sectors will follow a progressive rehabilitation programme including resistance exercise. Progression of resistance follows the national guideline for hip fractures which suggests resistance is added at 3 sets of 15 unweighted repetitions and progresses to 3 sets of 8 repetitions maximum [7]. For patients with a CAS ≥ 4, rehabilitation in a municipal rehabilitation centre will be recommended; alternatively, the resistance exercises will be performed at home with wrist weights. Except for the sit-to-stand exercise, the older adults will be requested to perform the exercises as often as possible, preferably three times a week. The exercise sit-to-stand as many times as possible will be recommended after each of the three main meals a day [15].

In the municipalities, nurses will visit the older adults on the third day after discharge to measure vital signs. Vital signs consist of early detection of illness or complications and pain management, e.g. blood pressure, pulse, respiratory frequency, saturation, consciousness, temperature, and saturation combined with measurement of C-reactive protein and haemoglobin.

An empowerment-orientated practice requires a change in the healthcare professionals’ approach towards seeing the older adults as a partner capable of acting and taking responsibility [16]. To implement the empowerment-orientated praxis, two initiatives are used: first, the patients will be given access to knowledge [16]. The older adults will receive a trolley containing the rehabilitation regime, exercise equipment, and a guide, targeted patient and next-of-kin to a digital healthcare app. The app contains videos and informative interviews with doctors and nurses from the ortho-geriatric ward and health professionals from the municipalities [17, 18]. Second, health professionals will participate in a workshop where they will learn about empowerment and how to use it. During the workshop, the health professionals will also be informed on the importance of strength training and measuring vital signs and pain and introduced to the rehabilitation regime. The intervention is described using the Template for Intervention Description and Replication (TIDieR) [19] (Table 2).

**Table 2 Tab2:** Description of intervention and comparator using TIDieR

	Rehabilitation for life	Usual rehabilitation and care
Why	Continuous and progressive rehabilitation as well as early detection of critical illness and complication during and after hospitalisation will improve the older adults’ physical performance and decrease mortality. Knowledge empowers older adults and facilitates a change in mindset among health professionals.	Activity-based rehabilitation restore and maintain the activities of daily living. Older adults’ need to regain functions creates motivation.
What	25 rehabilitation sessions with a physiotherapist over 12 weeks of these 5 within 2 weeks from discharge are planned. A virtual meeting between physiotherapist in the primary and secondary sectors and older adults is conducted in the 2 rehabilitation sessions after discharge. The suitcase contains knowledge and equipment the older adults need to take responsibility and perform daily exercises. Health professionals participate in a workshop. Early detection of critical illness and complications performed day 3 after discharge.	Older adults’ general amount of rehabilitation is approximately 1–2 rehabilitation sessions a week for 6–8 weeks. Care has to be prescribed.
Who provide	Physiotherapists, nurses, and social- and health assistants.	Physiotherapists, nurses, and social- and health assistants.
How	Face to face, virtual meetings, and app	Face to face.
Where	Ortho-geriatric ward, the patients’ home, and in the rehabilitation centres.	Ortho-geriatric ward, the patients’ home, and in the rehabilitation centres.
When and how much	*Weeks 1–2 after discharge:* *-* Five training sessions with a physiotherapist, duration up to 60 min. -One virtual meeting duration 30 min. -Vial measurements, duration up to 45 min. If necessary, one follow-up meeting with the municipal emergency nurse assessment, duration up to 45 min. Week 3 to week 12 after discharge: 2 weekly rehabilitation session with a duration up to 45 min is planned.	*During admission*: rehabilitation in the ortho-geriatric consist of a daily session with a physiotherapist duration of 30 min. *Week 1 after discharge:* -1 rehabilitation session duration up to 45 min. *Weeks 2–8 after discharge:* -1 or 2 weekly sessions of rehabilitation duration 45 min.
Tailoring	Patients with a CAS score ≥ 4 receive rehabilitation at a rehabilitation centre. Progression follows the national guidelines [7].	The patients rehabilitate at home or at a rehabilitation centre, pending on an individual assessment.

